#### Secondary Outcomes

Class-specific adherence (defined as a dichotomous outcome) will also be independently defined as PDC ≥80% for a given drug class at 1 year from discharge. Class-specific medication persistence (defined as a dichotomous outcome) will also be independently defined as having claims for any type of medication within that class from discharge date through the following 365 days with no period of 30 days or more without supply (ie, a discontinuation). The number of unique cardiac medication classes (range, 1-4) filled by a patient at their index fill will also be modelled to investigate whether either intervention meaningfully altered the number of medication classes per patient. Additionally, at the time of a patient’s index fill, we will measure the number of days supplied per medication class and the average number of days supplied across all unique medication classes — both outcomes will be dichotomized (ie, ≥90 days supplied versus <90 days supplied).

In addition to medication adherence–based and persistence-based outcomes, we will assess health care utilization and adverse clinical outcomes at 365 days from discharge including the frequency of outpatient primary care visits, frequency of outpatient cardiology visits, hospitalization for cardiovascular disease, hospitalization due to repeat acute MI, hospitalization due to stroke, repeat cardiac catheterization, coronary revascularization, and death. For both visit-based outcomes, visits occurring on the same day as discharge will be excluded.

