### Recruitment

Our study population will consist of patients aged 65 years and older who were discharged home from an Ontario hospital between September 1, 2015 and August 31, 2018 following a cardiac catheterization post-MI with evidence of CAD [29]. First, we will identify any CCN-CR claims for a cardiac catheterization with the primary referral reason being a ST-elevation myocardial infarction (STEMI) or non-STEMI with evidence of CAD, defined as left main artery stenosis ≥50% or major epicardial coronary artery stenosis ≥70% (Multimedia Appendix 1) [29]. Patients will be excluded if they meet any of the following criteria: site of procedure missing on their index claim, invalid or missing health card number, non-Ontario resident, <65 years of age (ie, patients who are not automatically eligible for ODB due to age) or ≥105 years of age, or died prior to discharge. Lastly, we will restrict to patients who filled a prescription for at least one medication from one of the 4 recommended cardiac medication classes (ie, statin, beta blocker, angiotensin system inhibitor, or secondary antiplatelet) within 7 days of discharge. This 1-week window was specified based on pre-intervention data, which determined that 93.4% of patients meeting all other exclusion criteria filled at least one recommended cardiac medication within 7 days (with 87.2% having their first fill within 1 day of discharge). We will herein refer to this initial prescription fill as a patient’s index fill. If patients have multiple eligible index cardiac catherization claims within the accrual window — an uncommon occurrence based on pre-intervention data — we only include the patient’s first claim (ie, earliest by date). Figure 4 fully summarizes the application of eligibility criteria to accrue study participants within the pre-intervention period.

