### Outcome Measures

#### Primary Outcome

The primary outcome will be long-term cardiac medication adherence assessed at 365 days from discharge. To calculate the primary outcome per patient, first we will identify the number of unique cardiac medication classes (out of 4) — statins, beta blockers, angiotensin system inhibitors, and secondary antiplatelets (ie, prasugrel, clopidogrel, or ticagrelor) — that were dispensed, as per ODB claims on the patient’s index fill date. The PDC will then be calculated per class [30,31], as it is generally a more conservative measure of adherence than the medication possession ratio [30,32]. If patients have 2 or more filled prescriptions for drugs in the same medication class with overlapping days supplied, we will assume the supply was used in sequence, as multiple doses of a drug in the same class would not typically be administered simultaneously [33]. The sum of class-specific PDC values across all classes will then be derived for each patient. Patients with an average PDC ≥80% among those medication classes dispensed at their index fill will be considered as adherent to their cardiac medication regimen [34]. For patients who die during their 1 year of follow-up, their PDC per class will be calculated over the time elapsed (in days) between their index fill and death date. It is not expected that this intervention will increase the number of cardiac medications prescribed to post-MI patients at the time of discharge but rather improve the long-term adherence to the cardiac medications initiated at discharge.

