#### Secondary Outcome Analysis

Consistent with the secondary analyses of the primary outcome described in the preceding section, all secondary outcomes will be analyzed using patient-level segmented regression analyses with terms for time, intervention, time after intervention, and the following covariates: age, sex, type of MI, prior MI, prior cardiac medication use, and site. The remaining secondary outcomes (time to hospitalization for cardiovascular disease, hospitalization due to repeat acute MI, hospitalization due to stroke, repeat cardiac catheterization, coronary revascularization, and death) will be analyzed at the patient level using Cox proportional hazards regression. Death will be treated as a censoring event for analyses of nonfatal, time-to-event outcomes.

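### Class-specific persistence runs to day 365 with no stop at death, unlike PDC, so many patients fully supplied until death would be scored as discontinued

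*Protocol article*

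**What the plan says.** All references are to the protocol article.

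- **Persistence (Secondary Outcomes).** "Class-specific medication persistence (defined as a dichotomous outcome) will also be independently defined as having claims for any type of medication within that class", over a window running "from discharge date through the following 365 days with no period of 30 days or more without supply (ie, a discontinuation". The definition does not mention death.
- **PDC (Primary Outcome).** Death is handled explicitly: "For patients who die during their 1 year of follow-up, their PDC per class will be calculated over the time elapsed", running from index fill to the date of death.
- **Class-specific adherence (Secondary Outcomes).** It is "independently defined as PDC ≥80% for a given drug class at 1 year from discharge", so it rests on the same per-class PDC and takes over its stop at death.
- **Cohort (Recruitment).** The only death-related exclusion is for patients who "or died prior to discharge". Patients who die later stay in the persistence denominator.
- **Analysis (Secondary Outcome Analysis).** "all secondary outcomes will be analyzed using patient-level segmented regression analyses with terms for time, intervention, time after intervention", plus patient covariates; the remaining clinical events go to Cox models. The one rule on death is "Death will be treated as a censoring event for analyses of nonfatal, time-to-event outcomes". Persistence is not a time-to-event outcome here, so that rule does not reach it.

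**The concern.** Two neighbouring outcomes built from the same dispensing records treat the same patient in opposite ways. Someone who refills every drug on time and dies on day 100 is fully adherent, because PDC stops at death. Under the persistence wording, the days from the end of the last supply to day 365 form a long gap, and the patient is labelled a discontinuation.

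Two things are at stake. First, persistence becomes a mixture of stopping treatment and dying, although death is already a separate secondary outcome. Second, whether a death is absorbed or counted as a gap depends on how far the last fill extends past it. Fill length is what the intervention changes, so the error need not be the same before and after September 2017, or across groups.

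**Working it through.** There is no figure in the plan to reproduce, since this concerns an outcome definition. The check applies the literal rule to a patient who is fully supplied until death.

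**Inputs from the article.** Window of 365 days; a gap of 30 days or more is a discontinuation; overlapping supply is carried forward (Primary Outcome); the revised form defaults to 90-day fills (Standardized Discharge Prescription Forms); no more than 54% of MI patients already receive 90 days or more (Rationale and Study Objectives).

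**Assumptions.** First fill on the day of discharge. Fill length L days, each refill collected e days early. One-year mortality m and the timing of deaths are not given, so ranges are shown.

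**Step 1: cut-off day.** A final gap of at least 30 days means supply ends on or before day 365 − 30 = 335. That allows n = floor(335/L) fills. The patient is scored as discontinued if death comes before the next fill would have been collected, on day D = n(L − e).

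- L = 30, on time: n = 11, D = 330.
- L = 90, on time: n = 3, D = 270.

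**Step 2: share of fully supplied decedents scored as discontinued.** Even deaths: D/365. Front-loaded (half in the first 90 days, the rest even): 0.5 + 0.5(D − 90)/275. Late-weighted (density rising linearly): (D/365)².

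| L, refill timing | D | Even | Front-loaded | Late-weighted |
|---|---|---|---|---|
| 30, on time | 330 | 90.4% | 93.6% | 81.7% |
| 60, on time | 300 | 82.2% | 88.2% | 67.6% |
| 90, on time | 270 | 74.0% | 82.7% | 54.7% |
| 100, on time | 300 | 82.2% | 88.2% | 67.6% |
| 30, 7 days early | 253 | 69.3% | 79.6% | 48.0% |
| 60, 7 days early | 265 | 72.6% | 81.8% | 52.7% |
| 90, 7 days early | 249 | 68.2% | 78.9% | 46.5% |
| 100, 7 days early | 279 | 76.4% | 84.4% | 58.4% |

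Examples, on-time refills. Death on day 100 with 90-day fills: supply ends on day 180, leaving 185 days, so discontinued, with truncated PDC of 100%. Death on day 310: with 30-day fills supply ends on day 330 (35-day gap, discontinued); with 90-day fills it ends on day 360 (5-day gap, persistent).

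**Step 3: loss in the persistence proportion** (even deaths, on-time refills), at most m × share:

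| Assumed m | 30-day fills | 90-day fills | Difference |
|---|---|---|---|
| 5% | 4.5 points | 3.7 points | 0.8 |
| 10% | 9.0 points | 7.4 points | 1.6 |
| 15% | 13.6 points | 11.1 points | 2.5 |

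**Step 4: possible bias in the intervention effect.** The difference above supposes that every patient moves from 30-day to 90-day fills. If 54% already have 90 days or more, 46% can move: m × (0.904 − 0.740) × 0.46 = 0.38, 0.76 and 1.13 points at m = 5%, 10% and 15%, with complete uptake. With late-weighted deaths the bracket is 0.817 − 0.547 = 0.270, giving 0.6 to 1.9 points. With refills a week early and even deaths it is 0.693 − 0.682 = 0.011, giving under 0.1 point.

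**Step 5: direction.** The share does not fall steadily with fill length. It is the same for 60-day and 100-day on-time fills. With early refills it is higher for 100-day fills (76.4%) than for 30-day fills (69.3%). It depends on how the fill length divides the year.

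**Step 6: after the fix.** If the window ends at the earlier of death or day 365, none of these fully supplied patients is scored as discontinued.

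**The case against.** The strongest reply is that the article is silent on death for persistence rather than stating that decedents fail. It is a condensed publication, a fuller plan may contain a stopping rule, and discontinuation naturally means stopping while alive. This is a fair limit: a reader might infer that the investigators intend to count death as discontinuation, and nothing in the text says so. What remains is that the article fixes a definite window and gap rule, and deals with death for PDC and for the Cox outcomes but not here. Applied as written, the rule gives the wrong answer for these patients.

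Other objections stand and limit the size:

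- The losses in Step 3 are upper bounds. Decedents who had already stopped are non-persistent under either rule and add no error.
- A misclassification that is stable over time lowers the level in both periods and largely cancels from the level and slope changes. Covariate adjustment also absorbs some case-mix drift. Only a change in the misclassification biases the effect.
- A reader might argue that a dichotomous outcome cannot accommodate death. That fails: class-specific adherence is dichotomous and is truncated at death.
- Truncation is not perfectly neutral. A patient who never refills is persistent by construction if death comes before about day 60 (30 days of supply plus a 30-day gap) or day 120 (90 plus 30), which also favours longer supplies.

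**Conclusion.** The inconsistency is real and should be corrected. Read literally, the rule scores many fully supplied decedents as discontinued: 90% with 30-day fills and 74% with 90-day fills under even deaths and on-time refills, and about half when deaths come late and refills are early. Under the even-deaths assumption the persistence proportion is lowered by at most about 0.90 or 0.74 times an unreported one-year mortality.

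Some bias in the intervention effect is possible. With mortality of 5% to 15%, even deaths, on-time refills, a move from 30-day to 90-day fills and 54% of patients already at 90 days or more, it is about 0.4 to 1.1 points at most. The 54% is itself stated as a maximum, so a lower baseline would leave more patients to move; incomplete uptake works the other way.

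A reader might infer that the rule systematically favours the intervention, by up to 2.5 points. The documents do not support that: the figure needs 15% mortality and a complete switch from 30-day to 90-day fills, and the direction reverses for some fill patterns. Nor do they support saying that most decedents are misclassified whatever the pattern. The primary outcome and class-specific adherence use the PDC truncated at death and are unaffected.

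**What to change.** In Secondary Outcomes, end the persistence window at the earlier of death or day 365, so that a patient with no gap of 30 days or more while alive is persistent. This matches the rule already given for PDC. State alongside it that patients who die early have little opportunity to show a gap. As a sensitivity analysis, report time to discontinuation with death as a competing event.

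The cost is one or two sentences in the outcome definition and one extra analysis. Dates of death are already among the linked data, through the Registered Persons Database (Data Sources). The price is that persistence in decedents rests on a shorter observation period.

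### Repeat catheterization and coronary revascularization are counted without setting aside procedures already planned at the index stay, which later adherence cannot change

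*Protocol article*

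**What the plan says.** Secondary Outcomes states that "we will assess health care utilization and adverse clinical outcomes at 365 days from discharge". The list that follows includes cardiovascular hospitalization, repeat MI and "hospitalization due to stroke, repeat cardiac catheterization, coronary revascularization, and death". The two procedures carry no qualifier such as unplanned, urgent or ischemia-driven, and no blanking period is given. The one exclusion rule in that section covers clinic visits: "For both visit-based outcomes, visits occurring on the same day as discharge will be excluded".

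Secondary Outcome Analysis models each of these events separately: "repeat cardiac catheterization, coronary revascularization, and death) will be analyzed at the patient level using Cox proportional hazards regression". Its only special event rule is "Death will be treated as a censoring event for analyses of nonfatal, time-to-event outcomes". No composite is specified.

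Under Recruitment, every patient enters after a catheterization for MI that shows obstructive disease, defined as "left main artery stenosis ≥50% or major epicardial coronary artery stenosis ≥70" per cent. The caption of Multimedia Appendix 1 covers identification of the index catheterization only, not the outcome events.

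**The concern.** The angiogram that makes a patient eligible is also the one from which any further procedure would be planned. A second procedure booked during the index stay was decided before the discharge prescription was filled, so a year of better or worse adherence cannot prevent or cause it. Under the outcome list as worded, it still counts as a repeat catheterization or a revascularization. It may also count as a cardiovascular hospitalization if elective admissions are included there. If the Cox models use the first event, as is usual, a planned procedure would also end that patient's time at risk and hide a later procedure that adherence might have influenced.

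What is at stake is how these secondary results are read. A ratio near 1 could mean that longer prescriptions did nothing for repeat procedures, or that many counted procedures were never open to change. The article's Discussion includes revascularization in the major adverse cardiac events that it expects better adherence to reduce, so the outcome is meant to carry clinical weight.

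**Working it through.** **Inputs**
- Relative reduction of 6.7%, so a ratio of 1 − 0.067 = 0.933 (Discussion). That figure is for major adverse cardiac events per 10% increase in adherence. Using it for unplanned procedures is an assumption.
- One-year event rate of 14.7% and about 3000 MIs a year in the region (Discussion).
- Planned share f of counted procedures: not in the article. Assumed values are 10%, 25% and 50%.

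**The article's own clinical figure**

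3000 × 0.147 × 0.067 = 29.5, which agrees within rounding with the stated number of just over 30 events prevented per year. The article gives no rate, event count or power for repeat catheterization or revascularization.

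**Dilution**

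If a share f of the counted procedures is planned and has a true ratio of 1, and the rest have ratio HR, then

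observed ratio = f + (1 − f) × HR.

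This is exact for event rates. It holds approximately for a Cox model if f is roughly constant over the year.
- f = 10%: 0.10 + 0.90 × 0.933 = 0.940
- f = 25%: 0.25 + 0.75 × 0.933 = 0.950
- f = 50%: 0.50 + 0.50 × 0.933 = 0.967

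The fraction of the effect lost is (observed − HR)/(1 − HR) = f. The loss is therefore the assumed planned share itself and not a separate result.

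**Cost in sensitivity**

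Schoenfeld's formula with two-sided 5% significance, 80% power and equal groups gives the number of events needed. The study's groups are not equal, so only the relative change is informative.
- no planned procedures: 6528 events
- f = 10%: 8117 (1.24 times)
- f = 25%: 11,812 (1.81 times)
- f = 50%: 27,041 (4.14 times)

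**Which outcomes are touched**

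The events are modelled one by one, so the dilution reaches the two procedure outcomes and, if elective admissions count, cardiovascular hospitalization. It does not reach repeat MI, stroke or death. The primary outcome is built from dispensing claims and is not touched.

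**The case against.** The strongest objection is that this is a condensed article. It gives no codes or event definitions for any clinical outcome, and a full protocol or analysis plan may contain a rule on planned procedures. That stands as a limit on severity. Even so, the article does fix the outcome names, the one-year window, the model, the censoring rule and one exclusion, and the set as it stands admits planned procedures.

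Second, the list is introduced as utilization as well as adverse outcomes, and an all-procedure count is a legitimate utilization measure. This also stands, and is a reason to keep that count as a supplementary result.

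Third, the study cannot measure effects of this size on these outcomes anyway. Take the 60 patients per month per site from the Power Calculation, 36 months and an assumed 8% unplanned rate. Group 1 (2 sites) then has 60 × 2 × 36 × 0.08 ≈ 346 events and group 2 (4 sites) about 691. With one-third of events after the intervention, the standard error of the log hazard ratio is 1/√(346 × 1/3 × 2/3) = 0.11 and 0.08 respectively. The shift from 0.933 to 0.967 is about 0.035 on the log scale, less than half of either. So the fix makes the estimates mean what they should, but it does not make them precise.

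A reader might infer that differences in staging practice between cardiac centers would appear as an intervention effect. The documents do not support that for stable differences: each group is compared with its own pre-intervention period, and site is a listed covariate. A province-wide change is what the parallel control group is meant to expose, although the article describes that comparison for the primary outcome.

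**Conclusion.** The point holds for repeat catheterization and coronary revascularization, and conditionally for cardiovascular hospitalization. Procedures planned at the index stay are not set aside, and they pull these ratios toward 1 in proportion to their share. With a true ratio of 0.933, the measured ratio lies between 0.940 and 0.967 for planned shares of 10% to 50%. Both the share and the transfer of the 6.7% figure to procedures are assumptions.

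Three stronger readings are tempting but not supported. The first is that the clinical endpoints as a whole are diluted: repeat MI, stroke and death are analysed separately and are unaffected, as is the primary outcome. The second is that a particular fraction of the effect is known to be lost: the article gives no staging rate, so any such fraction only restates the assumed share. The third is that the before-after comparison is biased: a stable planned share costs sensitivity only. Bias would need a change in staging specific to one group around September 2017, and the article gives no sign of one.

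**What to change.** In Secondary Outcomes:
- Do not count a repeat catheterization or revascularization whose CCN-CR referral date is on or before the index discharge date. Use the referral reason to support the classification. Keep the patient at risk for later procedures.
- Exclude admissions made only for such procedures from cardiovascular hospitalization.
- Report the all-procedure counts as a utilization measure or sensitivity analysis.

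No new data are needed. Data Sources lists the referral date among the registry's fields, and Recruitment already uses the referral reason to identify index cases. The cost is a smaller number of counted events, so wider intervals around a less diluted estimate, and some misclassification where referral dates or reasons are poorly coded. The all-procedure analysis would show how much the classification matters.

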### Statistical Analysis

#### Primary Outcome Analysis

Our primary analytical approach will use segmented linear regression analyses of the aggregate monthly data in each group. To promote stability of the time series, we will pool data across the hospitals within each intervention group (ie, standardized discharge prescription forms plus education [intervention group 1] or education only [intervention group 2]). Within each of the 2 intervention groups, we will then independently analyze the aggregated monthly proportions of patients adherent to their cardiac medication regimen at 1 year (expressed as a percentage) using segmented linear regression. In case of nonlinearity of the monthly series, segmented logistic regression analysis of the monthly proportions will be used. Terms will be included for time (in months; treated as continuous [range, 0-35]), intervention (an indicator denoting observations from the post-intervention window), and time post-intervention (defined as time-23 if observation from post-intervention period; 0 otherwise) [35,36]. Serial autocorrelation will be accounted for using first-order autoregressive errors. Visual assessment of model residuals plotted against time will be used to assess goodness of fit. Intervention effects estimated using segmented linear autoregressive error models will be expressed as absolute post-intervention changes in the intercept and slope with corresponding 95% CIs. Post-intervention changes in intercept (or level) and slope (or trend) can respectively be interpreted as the immediate and gradual effects of the intervention on the primary outcome over time [35,36]. Additionally, we will express the overall intervention effect (ie, as combined intercept and slope changes) at the end of the study, on the absolute scale, by comparing the fitted post-intervention trend to the projected secular trend in the final month of observation [35].

The aforementioned segmented regression analyses will compare pre-intervention to post-intervention levels and trends within intervention groups; therefore, groups will act as their own internal controls. Additionally, we will compare these changes to changes observed in the control group (ie, all other hospitals in Ontario). Analysis of the parallel control group — which will be identically specified to the intervention group analyses — will help address threats to internal validity, such as co-occurring interventions or other policy changes that could be rival explanations for any observed changes in our intervention series. In other words, if we detect a post-intervention effect in the parallel control group, it suggests that changes in the underlying patient population or another (unidentified) intervention could have occurred around the same time across Ontario hospitals that might explain away any observed intervention effects.

To account for potential differences in patient case mix over time and among sites, we will conduct additional secondary analyses of the primary outcome with the patient as the unit of analysis. We will use segmented binary logistic regression analysis with terms as specified in previous paragraphs and with the addition of the following patient covariates: age, sex, type of MI (STEMI vs non-STEMI), prior MI, prior cardiac medication use, and site.

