## Methods

### Trial Setting and Design

The Myocardial Infarction Prescription Adherence Duration (MIPAD) study will use a quasiexperimental, interrupted time series design to evaluate the impact of standardized prolonged discharge prescription forms and education versus usual care on long-term cardiac medication adherence among elderly, post-MI patients in Ontario who were discharged from hospital following a cardiac catheterization procedure between September 1, 2015 and August 31, 2018.

After the first 24 months within the study window (ie, the pre-intervention period: September 1, 2015 through August 31, 2017), a total of 6 sites (2 of which are cardiac centers, where advanced cardiac procedures are performed in Ontario) across 3 hospital corporations (Hamilton Health Sciences [HHS], St. Joseph’s Healthcare Hamilton, and Niagara Health System [NHS]) were nonrandomly allocated to receive at least one of the two planned intervention packages for the subsequent 12 months (ie, the post-intervention period: September 1, 2017 through August 31, 2018; Figure 2). These 6 intervention sites were chosen as a convenience sample based on the investigators’ affiliations. Irrespective of intervention package received (detailed fully in the following sections), all interventions were implemented starting September 1, 2017 at each of these sites. All 6 intervention sites are within the same health care region in southwest Ontario, Canada, which serves approximately 1.4 million people. All other Ontario hospitals will collectively act as a contemporaneous control group [23,24].

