#### Power Calculation

Using the simulation approach developed by Zhang et al [37], we determined that 24 pre-intervention and 12 post-intervention data points (collected at monthly intervals) in each of the 2 intervention groups will achieve 80% power to detect an immediate absolute increase (ie, intercept change) of 10% in the monthly proportion of patients deemed adherent to their recommended cardiac medications using a likelihood ratio test at the 5% level of significance. The anticipated baseline proportion of patients with cardiac medication adherence (ie, average PDC ≥80%) is 75%. The simulation assumed a mean square error for the monthly proportions of 3.1% with 60 patients per month per site, a pre-intervention trend of 0, and an autocorrelation parameter of 0.3.

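### With 36 monthly points, the stated 5% likelihood ratio test for the level change rejects a true null about 10-11% of the time, and the usual AR(1) 95% intervals also under-cover

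*Protocol article*

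**What the plan says.** Under Primary Outcome Analysis, each intervention group's monthly adherence percentages are modelled with an intercept, time (0 to 35), a post-intervention indicator and a post-intervention time counter. On the errors, the section says "Serial autocorrelation will be accounted for using first-order autoregressive errors". Level and slope changes are reported with 95% CIs, and the level change is read as the immediate effect. No estimator, degrees of freedom or hypothesis test is named there. The control series gets the same model.

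Under Power Calculation the design is "24 pre-intervention and 12 post-intervention data points (collected at monthly intervals) in each of the 2 intervention groups". It "will achieve 80% power to detect an immediate absolute increase (ie, intercept change) of 10" percentage points, "using a likelihood ratio test at the 5% level of significance". The inputs are a baseline of 75%, a pre-intervention trend of 0, an autocorrelation of 0.3 and a "mean square error for the monthly proportions of 3.1% with 60 patients per month per site".

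The counter is "time post-intervention (defined as time-23 if observation from post-intervention period; 0 otherwise"). Under Trial Setting and Design, "all interventions were implemented starting September 1, 2017 at each of these sites", which is month index 24.

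**The concern.** An AR(1) model with four mean terms leaves little information in 36 points to estimate the autocorrelation. ML estimates it too low, so the standard error of the level change is too small. The chi-square and normal references do not allow for this uncertainty. If the stated 5% level does not hold, a chance shift in either intervention series is declared an effect too often. The identically specified control series is also affected. It serves as the check on rival explanations, so a false level change there could be used to dismiss a real intervention effect.

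**Working it through.** **Inputs.** From the protocol: 24 + 12 = 36 points, autocorrelation ρ = 0.3, a 1-df likelihood ratio test at 5%, and time coded 0-35 with the time-23 counter. Assumed: stationary Gaussian AR(1) errors and exact ML.

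**Model.** y(t) = b0 + b1·t + b2·P(t) + b3·(t − 23)·P(t) + e(t), with P = 1 for t ≥ 24 and e(t) = ρ·e(t−1) + u(t). The statistic is LR = 2·(log-likelihood with b2 − log-likelihood without b2), rejecting above 3.84.

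**The protocol's own figure first.** The stated 80% power for a 10-point step could not be reproduced, because the scale of the mean square error of 3.1% is unclear:

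- Binomial variance at 60 per month is 0.75 × 0.25 / 60 = 0.003125, an SD of 5.59 points. Power of the nominal test is 59-62%.
- At 120 per month it is 0.75 × 0.25 / 120 = 0.00156, an SD of 3.95 points. Power is 84-86%.
- Read as an SD of 3.1 points, power is 96-97%. Read as a variance of 0.031, it is 17-18%.
- An SD of about 4.4 would give 80%, but no stated reading yields it.

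This does not affect the null results below, because under the null the test does not depend on the residual scale.

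**Null rejection of the likelihood ratio test (nominal 5%), 10,000-20,000 series per setting:**

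| True ρ | Rejection |
|---|---|
| 0 | 9.2% |
| 0.1 | 9.8% |
| 0.3 | 10.7% |
| 0.5 | 11.7% |

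Simulation error is about √(0.107 × 0.893 / 10,000) = 0.003, or 0.3 points. Standard time-series software gave 10.0% in 400 series at ρ = 0.3. Independent binomial counts of 60, 120 or 240 per month gave 9.1-9.5%. The cutoff that gives a true 5% at ρ = 0.3 is about 5.6-5.7.

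**Miss rate of a nominal 95% interval for the level change, ρ = 0.3:**

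| Method | Misses |
|---|---|
| ML, normal reference | 13.6% |
| ML, corrected SE, t(32) | 10.3% |
| Yule-Walker, t(32) | 11.1% |
| Prais-Winsten, t(32) | 11.0% |
| REML, t(32) | 7.5% |
| ρ known, t(32) | 5.2% |

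The last row identifies the cause: when ρ need not be estimated, the level is held. The ML estimate of ρ averages 0.13 when the truth is 0.3. The software's default Wald interval, which uses a different standard error, missed 7.0% of the time in its 400 series. That figure is imprecise: √(0.07 × 0.93 / 400) = 0.013.

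**With a calibrated cutoff.** Taking the cutoff from simulation at each series' estimated ρ brings rejection to 5.6%. Power for a 10-point step, with the time-23 counter, is then 46% at SD 5.59, 75% at SD 3.95 and 92% at SD 3.1.

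**The counter.** At t = 24 it equals 24 − 23 = 1, so the fitted effect in September 2017 is b2 + b3, and b2 alone is the fitted gap at index 23 (August 2017). With ρ = 0.3 the standard error of the level term is 0.866 residual SDs under time-23 and 0.816 under time-24: (0.866 − 0.816) / 0.866 ≈ 6% smaller. Rejection under the null stays near 11% with either coding.

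**The case against.** The strongest objection is that the faulted procedure is only partly fixed by the protocol. The likelihood ratio test appears only in the power section. The primary analysis section promises AR(1) errors and 95% CIs, and an article may leave the estimator and degrees of freedom to the analysis plan. This stands to the extent that the missing estimator is not itself a fault. A reader might also infer that the primary analysis as a whole runs at twice its error rate. The documents do not support that: doubling applies to the named test with a chi-square reference, while a REML interval would miss about 7.5%. The objection does not rescue the stated level, because every estimated-autocorrelation method tried came out above 5%.

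A reader might further infer that the stated 80% power is inflated by this fault. That cannot be shown, since the simulation behind it is not visible and its figure was not reproduced.

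On the counter, it is tempting to say that the effect is estimated a month before launch. That is too strong. Each point averages a month of discharges, so a September 1 launch falls between the August and September points. The coding is common, leaves the fitted values and end-of-study effect unchanged, and gives the same coefficient for a pure step change.

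**Conclusion.** The point holds for the test that the protocol states: at its own inputs, nominal 5% is about 10-11% in practice. For the promised 95% CIs the shortfall depends on an unstated choice, from about 7.5% missed (REML with t) to about 14% (ML with a normal reference). This rests on Gaussian AR(1) errors and the four-term model; it does not rest on the unclear residual error. It should be corrected, because the remedy needs no new data. The time-23 counter is a minor, separate matter of precision and interpretation, and does not cause the inflation.

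**What to change.** State the estimator: REML for the autocorrelation and standard errors, with small-sample degrees of freedom. Because REML with t(32) corrects only part of the problem, take the p value and CI for the level change from a parametric bootstrap of the 24+12 design at the estimated autocorrelation. If the likelihood ratio test is kept, compute it by ML, since REML likelihoods are not comparable between different mean models, and use the simulated cutoff (about 5.6-5.7 at 0.3). Apply the same method to the control series. State the scale of the mean square error and restate power under the calibrated test.

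Separately, code the counter as time-24 so that the level change is the September 2017 effect, or keep time-23 and say that the effect in that month is level plus one slope unit.

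The cost is a few lines of code and wording, lower stated power and wider intervals. As a rough guide, an interval from the likelihood ratio widens by √(5.65 / 3.84) ≈ 1.21, or about a fifth.
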